#### Safety reporting

##### Adverse event reporting period

The reporting period during which AEs must be reported is the period from enrollment to the end of the study period (24 months). All unresolved AEs must be followed by the trial monitor in contact with the chief investigator and principal investigators until the events are resolved, the patient is lost to follow-up, or the AE is otherwise explained. At the last scheduled study visit, the trial nurse will instruct each patient to report any subsequent event(s) that the patient, or the patient’s personal physician, believes might reasonably be related to prior study treatment. Such events should be reported to the (previous) treating ophthalmologist at the department of ophthalmology of the trial site after the trial has ended. Patients who withdraw early from the study will be contacted by trial staff 30 days after their last visit, if the patient gives permission to do so, to ascertain whether any AEs have occurred.

##### *Definition of adverse events/reactions*

An *adverse event (AE)* or adverse experience includes any untoward medical occurrence in a patient or clinical investigation participant who has been administered a medicinal product, and this event does not necessarily have to have a causal relationship with this treatment (the study medication).

An AE can therefore be any unfavorable and unintended sign (including an abnormal laboratory finding), symptom or disease temporally associated with the use of the study medication, whether or not the event is considered related to the study medication.

In the case of an *adverse reaction (AR)*, a causal relationship between a study medication and an AE is at least a reasonable possibility (that is, the relationship cannot be ruled out).

All cases judged by either the reporting medically qualified professional or the sponsor as having a reasonable suspected causal relationship to the study medication qualify as adverse reactions.

These include all untoward and unintended responses to a medicinal product related to any dose.

ARs could include, for instance, nausea, hypertension, lower back pain*,* headache*,* arthralgia, intravenous injection site reactions (in the case of PDT), cough, pharyngitis, pneumonia, fever and flu-like symptoms, hypersensitivity and allergy reactions, vaso-vagal reactions, atrial fibrillation, angina, and sunburn after sunlight exposure in the first two days after PDT treatment.

#### Procedures for recording adverse events/reactions

All AEs occurring during the study observed by the investigator or reported by the participant, whether or not attributed to study medication, will be recorded on the CRF. The following information will be recorded: description, date of onset and end date, severity, assessment of relatedness to study medication, other suspect drug or device and action taken. Follow-up information should be provided as necessary. AEs considered related to the study medication, as judged by a medically qualified investigator or the sponsor, will be followed until resolution or until the event is considered stable. AEs considered related to the study procedure, as judged by a qualified investigator or the sponsor, will be followed until resolution or until the event is considered stable. All related AEs that result in a participant’s withdrawal from the study or are present at the end of the study, should be followed up if the patient gives consent to do so, until a satisfactory resolution occurs.

It will be left to the investigator’s clinical judgment whether or not an AE is of sufficient severity to require the participant’s removal from the trial. A participant may also voluntarily withdraw from treatment due to what he or she perceives as an intolerable AE. If either of these occurs, the participant must undergo an end-of-study assessment and be given appropriate care under medical supervision until symptoms cease or the condition becomes stable.

The relationship of AEs to the study medication will be assessed by a medically qualified investigator, and if necessary, discussed with the chief investigator. Any pregnancy occurring during the clinical study and the outcome of the pregnancy fathered by trial participants, should be recorded and followed up for congenital abnormality or birth defect.

#### Definitions of serious adverse events/reactions

A *serious adverse event (SAE)* is any untoward medical occurrence that at any dose accomplishes the following:Results in death,Is life-threatening, note: the term "life-threatening" in the definition of "serious" refers to an event in which the participant was at risk of death at the time of the event; it does not refer to an event that hypothetically might have caused death if it were more severe.Requires inpatient hospitalization or prolongation of existing hospitalization.Results in persistent or significant disability/incapacity, or is a congenital anomaly/birth defect.Other important medical events. Note: other events that may not result in death, are not life threatening, or do not require hospitalization, may be considered a SAE when, based upon appropriate medical judgement, the event may jeopardize the patient and may require medical or surgical intervention to prevent one of the outcomes listed above. In this trial, these events are mainly vision-related.

##### Vision-threatening adverse events/reactions

An AE is considered to be vision-threatening and is a reportable SAE if it meets one or more of the following criteria:It caused a decrease in visual acuity of >30 letters (compared with the last assessment of visual acuity prior to the most recent treatment) within the follow-up period of 7 to 8 months.It required surgical intervention.In the investigator’s opinion, it may require medical intervention to prevent permanent loss of vision. Causes for such vision-related AEs could include for instance: RPE tears, subretinal hemorrhage, choroidal neovascularization.

A *serious adverse reaction (SAR)* is an adverse event (expected or unexpected) that is both serious and, in the opinion of the reporting investigator, believed with reasonable probability to be due to one of the study treatments, based on the information provided.

A *suspected unexpected serious adverse reaction (SUSAR)* is a serious adverse reaction, the nature or severity of which is not consistent with the applicable product information (for example, the Investigator’s brochure for an unapproved investigational product or summary of product characteristics for an approved product).

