#### Reporting procedures for serious adverse events

The data monitoring committee (DMC) will undertake a review of all SAEs for the study. The DMC may hold electronic meetings. The DMC will meet at intervals and consider the following:The occurrence and nature of the adverse events.Whether additional information on the adverse events is required.Taking appropriate action where necessary to halt trials.Act/advise on incidents occurring between meetings that require rapid assessment (for example, SUSARs).

All SAEs will be reported to the DMC within one working day of discovery or notification of the event. All SAE information will be recorded on an SAE form, which will be sent electronically to members of the DMC. Additional information received for a case (follow-up or corrections to the original case) will be detailed on a new SAE form. After receiving the SAE report within one working day, the medical monitor will review possible SAEs weekly, and the DMC has a meeting every three months to review the SAEs, if present. The chief investigator will also report all SUSARs to the competent authorities (TOL/CCMO in the Netherlands, Bfarm in Germany, and ANSM (Agence Nationale de Sécurité du Médicament et des Produits de Santé) in France, the ethics committees concerned, and the host NHS trust in the United Kingdom. Fatal or life-threatening SUSARs will be reported within 7 days and all other SUSARs within 15 days. The Chief Investigator will also inform all investigators concerned of relevant information about SUSARs that could adversely affect the safety of participants.

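### A serious adverse reaction is defined more narrowly than an adverse reaction, so some suspected serious unexpected events fall outside SUSAR reporting

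*Protocol article*

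**What the plan says.** Under *Definition of adverse events/reactions*, the protocol article calls an event an adverse reaction (AR) when "a causal relationship between a study medication and an AE is at least a reasonable possibility (that is, the relationship cannot be ruled out"). It then adds who may decide: "All cases judged by either the reporting medically qualified professional or the sponsor as having a reasonable suspected causal relationship to the study medication" qualify. *Procedures for recording adverse events/reactions* again accepts the view of an investigator or the sponsor when it says which related events are followed to resolution.

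Under *Vision-threatening adverse events/reactions*, a serious adverse reaction (SAR) is an event that is serious and, "in the opinion of the reporting investigator, believed with reasonable probability to be due to one of the study treatments". The same section says that a SUSAR "is a serious adverse reaction, the nature or severity of which is not consistent with the applicable product information".

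Under *Reporting procedures for serious adverse events*, all SAEs go to the data monitoring committee (DMC) within one working day. The chief investigator reports SUSARs to authorities and ethics committees: "Fatal or life-threatening SUSARs will be reported within 7 days and all other SUSARs within 15 days". The chief investigator also passes relevant SUSAR information to the other investigators.

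**The concern.** The serious form of a reaction should be the general form plus a seriousness criterion. Here it also carries a stricter causality threshold and loses one of the two people entitled to judge causality. The stricter rule therefore applies to the events for which prompt outside notice matters most.

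The sole judge for a SAR is the reporting investigator. The trial is open-label (*Summary of trial design*), so that person knows the treatment given. The sponsor, who sees events from all five sites, has no stated say in the SAR classification.

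At stake is whether a suspected, serious, unexpected harm is reported on the expedited timetable to authorities and ethics committees in four countries, and passed on to the other sites.

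**Working it through.** No figure in the plan bears on this, so the check compares the definitions and follows an event through them.

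**Step 1. The two tests side by side**

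| | Adverse reaction | Serious adverse reaction |
|---|---|---|
| Threshold | reasonable possibility; link cannot be excluded | reasonable probability |
| Who judges | reporting professional or sponsor | reporting investigator |
| Cause considered | study medication | one of the study treatments |

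The first two rows make the SAR narrower than the AR. The third runs the other way. HSML uses no photosensitizing drug (*High-density subthreshold micropulse laser therapy*, Background), so on a literal reading the AR wording does not reach a laser reaction, while the SAR wording does.

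**Step 2. What depends on the SAR definition**

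A SUSAR is a SAR that is inconsistent with the product information. The 7- and 15-day reports and the notice to other investigators are stated for SUSARs. An event that fails the SAR test therefore triggers none of them.

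**Step 3. Four cases of a serious, unexpected event after half-dose PDT**

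| Case | Investigator's view | Sponsor's view | AR? | SAR? | SUSAR? |
|---|---|---|---|---|---|
| A | reasonably probable | any | yes | yes | yes |
| B | cannot be ruled out, not probable | any | yes | no | no |
| C | unrelated | suspects a link | yes | no | no |
| D | unrelated | unrelated | no | no | no |

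B and C are the gap. B depends on reading probability as a higher bar than possibility. If the two words were meant as synonyms, B would become a SUSAR. C would remain outside, because the SAR sentence does not mention the sponsor.

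**Step 4. Does another section close the gap?**

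- All SAEs, whatever their cause, reach the DMC within one working day, so events in B and C are seen.
- Under *Reporting procedures for serious adverse events* and *Trial safety group/data monitoring committee*, the DMC can act between meetings on incidents that need rapid assessment. SUSARs are given as an example in the first of these, and the second sets no such limit.
- Neither section says that the DMC, the medical monitor or the sponsor may classify an event as a SUSAR when the reporting investigator does not hold the SAR view. The expedited duty depends on that classification.

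The events are visible within the trial, but no stated rule sends them out on the expedited timetable.

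**The case against.** The strongest reply is that this is loose wording in one sentence of a condensed article, within a safety system that otherwise works. Every SAE reaches the DMC quickly, the between-meeting route is not confined to SUSARs, and the sponsor's judgement is kept for adverse reactions and related events without excluding serious ones. The point also leaves the primary endpoint, the sample size and the analysis untouched. All of that is correct, and it limits the consequence. It does not remove the conflict, because the article prints both definitions and they disagree. This is not a detail left to the full protocol.

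A second objection concerns the remedy. Defining a SAR simply as a serious AR would bring in the medication wording and could drop serious laser reactions in the HSML arm. That objection stands, and the fix below allows for it.

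A reader might also infer that SUSAR reports will be late, because "the medical monitor will review possible SAEs weekly" while the shortest deadline is 7 days. The article does not support this. It does not make the weekly review a precondition for the chief investigator's report, and it provides a rapid route. If one assumed that the weekly review were the only point of recognition, one working day (1 calendar day, or 3 over a weekend) plus a wait of 0 to 7 days gives 1 + 0 = 1 to 3 + 7 = 10 days. The upper end passes 7 days but stays within 15. If the clock starts when the report is received, the wait is 0 to 7 days and the limit is not passed. The article states neither the sole-step assumption nor when the clock starts.

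**Conclusion.** The inconsistency is real. The SAR definition uses a higher causality threshold and one judge, where the AR definition uses a lower threshold and either of two judges, and the SUSAR definition inherits the narrower test. The passages need to be reconciled.

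The reach is limited to serious, unexpected events that the site thinks only possibly related or that only the sponsor suspects. It would be wrong to infer that every SAE the site considers possibly related loses its expedited report: expected events were never SUSARs. The article gives no expected SAE rate, so no count can be put on the gap. Efficacy conclusions are unaffected.

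The conclusion assumes that staff follow the definitions literally. The threshold part also assumes that probability and possibility are meant as different standards. The single-judge part does not need that assumption. The conclusion does not extend to late reporting.

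**What to change.** Replace the SAR sentence under *Vision-threatening adverse events/reactions* with wording to this effect: *a serious adverse event for which a causal relationship to one of the study treatments (half-dose PDT or HSML) is at least a reasonable possibility, as judged by either the reporting investigator or the sponsor.* The SUSAR definition can stay as it is and will then follow correctly.

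Keep the reference to study treatments so that laser events remain covered. Bring the medication wording under *Definition of adverse events/reactions* into line with it, so that non-serious laser reactions also count as adverse reactions.

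The cost is a change of wording, with no new staff or data collection. The downside is a few more expedited reports, some of which will concern events later judged unrelated.

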#### Reporting procedures for serious adverse events

The data monitoring committee (DMC) will undertake a review of all SAEs for the study. The DMC may hold electronic meetings. The DMC will meet at intervals and consider the following:The occurrence and nature of the adverse events.Whether additional information on the adverse events is required.Taking appropriate action where necessary to halt trials.Act/advise on incidents occurring between meetings that require rapid assessment (for example, SUSARs).

All SAEs will be reported to the DMC within one working day of discovery or notification of the event. All SAE information will be recorded on an SAE form, which will be sent electronically to members of the DMC. Additional information received for a case (follow-up or corrections to the original case) will be detailed on a new SAE form. After receiving the SAE report within one working day, the medical monitor will review possible SAEs weekly, and the DMC has a meeting every three months to review the SAEs, if present. The chief investigator will also report all SUSARs to the competent authorities (TOL/CCMO in the Netherlands, Bfarm in Germany, and ANSM (Agence Nationale de Sécurité du Médicament et des Produits de Santé) in France, the ethics committees concerned, and the host NHS trust in the United Kingdom. Fatal or life-threatening SUSARs will be reported within 7 days and all other SUSARs within 15 days. The Chief Investigator will also inform all investigators concerned of relevant information about SUSARs that could adversely affect the safety of participants.

#### Trial safety group/data monitoring committee

The DMC will conduct a review of all SAEs for the study reported every 3 months and cumulatively, if present. The aims of this review will include the following:To pick up any trends, such as increases in unexpected/expected events, and take appropriate action.To seek additional advice or information from investigators where required.To evaluate the risk of the trial continuing and take appropriate action where necessary.To act or advise, through the chairman or other medical monitors, on incidents occurring between meetings that require rapid assessment.

This committee, which is based in the coordinating center in Nijmegen, will receive SAEs within one working day, and will analyze the available safety data and study data in a meeting every 3 months, if present.

### Description of statistical methods

#### Univariate analysis

##### *Analysis for the primary endpoint*

The purpose of this study is to identify the difference between the efficacy of the two treatment modalities based on the anatomical effect on OCT scan (absence of SRF versus still SRF visible). As we expect one treatment to be superior to the other, this study is designed to be a superiority study. Statistical analysis on the primary parameter will be performed by analyzing the relative risk by using a cross-table comparing evaluation at 6 to 8 weeks after treatment with baseline.

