### Objectives

#### Primary objective

The primary objective of this study is to investigate whether treatment of cCSC patients with macular SRF on optical coherence tomography (OCT) with half-dose PDT results in more eyes with an absence of SRF on the OCT as compared to HSML treatment.

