### Primary and secondary endpoints

#### Primary endpoint

The primary endpoint of this study is to assess if there is a difference between the efficacy of half-dose PDT treatment versus the HSML treatment in patients with cCSC. The assessment of this efficacy will be based on the anatomical effect on OCT: absence of SRF versus persistent SRF, 6 to 8 weeks after treatment. After all, the absence or presence of fluid under the retina on the OCT scan is a direct reflection of the activity of the disease in these patients.

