#### Inclusion criteria

The inclusion criteria are as follows:Male and female patients ≥18 years of age who are able to give written informed consent.Active cCSC.Subjective visual loss >6 weeks, interpreted as onset of active disease.SRF that includes the fovea on OCT scanning at baseline examination. *Note*: SRF does *no**t* have to include fovea on OCT to be eligible for treatment at control visit 1 as long as there is persistent SRF in the macula, which is interpreted as persistently active disease.Hyperfluorescent areas on ICG angiography.≥ 1 ill-defined hyperfluorescent leakage areas on fluorescein angiography with RPE window defect(s) that are compatible with cCSC.

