#### Multivariate analysis

##### Analysis for the secondary endpoints

For the secondary endpoints, the following analyses will be performed:Anatomic results based on OCT scan (absence of SRF versus persistent SRF) at evaluation point 1 will be compared to the baseline.Number of subsequent treatments needed in each treatment arm.Mean change from baseline in ETDRS BCVA in the study eye at 6 to 8 weeks after treatment and at the end evaluation will be compared between the two treatment modalities.Mean change from evaluation point 1 in ETDRS BCVA in the study eye at final evaluation among those with subsequent and those without subsequent treatment will be compared between the two treatment modalitiesMean change from baseline in retinal sensitivity in the study eye to 6 to 8 weeks after treatment will be compared between the two treatment modalities.Mean change from baseline in the NEI-VFQ-25 questionnaire to 6 to 8 weeks after treatment will be compared among the two treatment modalities.

The first two analyses will be performed by the use of a cross-table. Furthermore, the continuous secondary variables will be analyzed using an ANCOVA model with baseline as and treatment as factor. For categorical secondary endpoints, a chi-square test will be performed. In addition, a logistic model with baseline as covariate and treatment as factor will be performed. The change from baseline in the NEI-VFQ-25 questionnaire results will be summarized descriptively.

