#### Interim analysis

A formal interim analysis will be performed when 78 participants received the first evaluation at 6 to 8 weeks after treatment. Statistical analysis on the primary parameter will be performed by analyzing the relative risk by using a cross-table comparing evaluation at 6 to 8 weeks after treatment with baseline.

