#### The level of statistical significance

For the primary endpoint, the overall null hypothesis is as follows:

H_0_ : probabilities of success are the same in both treatment arms (π_1_ = π_2_)

*versus*

H_1_ : probabilities of success are different in the treatment arms (π_1_ ≠ π_2_)

For statistical testing, the significance level will be 0.05 unless specified otherwise.

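### The primary and interim analyses are written as a comparison of the 6-to-8-week evaluation with baseline, so as worded they do not test half-dose PDT against HSML

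*Protocol article*

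**What the plan says.** Under Analysis for the primary endpoint, the protocol article first gives a between-arm purpose. It then specifies the analysis as "analyzing the relative risk by using a cross-table comparing evaluation at 6 to 8 weeks after treatment with baseline". The Interim analysis section opens with "A formal interim analysis will be performed when 78 participants received the first evaluation at 6 to 8 weeks after treatment" and repeats the same analysis sentence word for word. Treatment arm is not named as a dimension of the table in either place.

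The rest of the design is between-arm:

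- **Primary objective:** whether half-dose PDT "results in more eyes with an absence of SRF on the OCT as compared to HSML treatment".
- **Primary endpoint:** "absence of SRF versus persistent SRF, 6 to 8 weeks after treatment".
- **The level of statistical significance:** the null is that "probabilities of success are the same in both treatment arms" and the alternative is that "probabilities of success are different in the treatment arms".
- **Number of participants:** 78 per arm for a difference of about 22 percentage points in favour of half-dose PDT.

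The Inclusion criteria require "SRF that includes the fovea on OCT scanning at baseline examination".

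Under Analysis for the secondary endpoints, the first item again sets the SRF result at evaluation point 1 against baseline. For categorical secondary endpoints the section adds a chi-square test and says that "a logistic model with baseline as covariate and treatment as factor will be performed".

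**The concern.** The stated analysis and the stated hypothesis concern different contrasts. A table of evaluation against baseline is a before-after comparison. It would not address a difference between arms even if baseline status varied. Here baseline status does not vary, because SRF is an entry requirement, so the table is also degenerate.

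The sentence fixes both the primary test and the only formal interim test. If it stands, the pre-specified analysis does not test the pre-specified null, and the actual between-arm test has to be settled later, in an open-label trial. This is not a detail left to an analysis plan that is not shown: the article does state the analysis, and states it wrongly.

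**Working it through.** **Inputs from the documents.** HSML success about 50%, planning difference 22 points, 78 per arm, two-sided alpha 0.05, power 80%, one O'Brien-Fleming interim (Number of participants; The level of statistical significance). Baseline SRF is present in 100% of eligible eyes (Inclusion criteria).

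**Assumptions.** The pair of rates behind the 22 points is not given; I take 50% versus 72% and vary it. The O'Brien-Fleming inflation factor for two looks is taken as 1.008 and the final-look alpha as 0.048.

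**1. Which comparison was the trial sized for?** For two independent proportions,

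n per arm = [1.96·√(2p̄(1−p̄)) + 0.842·√(p₁(1−p₁) + p₂(1−p₂))]² / (p₁−p₂)²

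- 50% versus 80%: p̄ = 0.65, n = 39 (plan: 40).
- 50% versus 72%: p̄ = 0.61, n = 76; 76 × 1.008 = 76.6, so 77 (plan: 78).
- Other 22-point pairs, with inflation: 70 (58% versus 80%) to 81 (39% versus 61%).
- Power at 78 per arm, 50% versus 72%: 0.810, or 0.806 at alpha 0.048.

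The plan's figure is therefore reproduced, within 2, as a test of PDT against HSML.

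**2. What does the table as written give?** Expected counts at 78 per arm are 0.50 × 78 = 39 cleared on HSML and 0.72 × 78 ≈ 56 cleared on PDT.

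| | SRF absent, baseline | SRF absent, evaluation | RR of absence vs baseline | RR of persistence vs baseline |
|---|---|---|---|---|
| HSML | 0/78 | 39/78 | (39/78)/(0/78), undefined | (39/78)/(78/78) = 0.50 |
| PDT | 0/78 | 56/78 | (56/78)/(0/78), undefined | (22/78)/(78/78) = 0.28 |
| Both arms | 0/156 | 95/156 | undefined | (61/156)/(156/156) = 0.39 |

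The baseline risk of SRF is 1, so the relative risk of persistence always equals 1 minus the success rate. With both arms in one table, the split between arms disappears: 22 + 39 persistent eyes and 30 + 31 persistent eyes both give 61/156 = 0.39, although the first split is the planned effect and the second is practically none.

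**3. What does the between-arm table give?** Arm by SRF status at evaluation visit 1, with 56/78 versus 39/78:

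- RR of absence = 56/39 = 1.44.
- SE of log RR = √(1/56 − 1/78 + 1/39 − 1/78) = 0.134.
- 95% CI = exp(0.362 ± 1.96 × 0.134), about 1.11 to 1.87.

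This table does address π₁ = π₂.

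**4. Does the secondary section supply the test?** It names treatment as a factor, but only for secondary endpoints. Its first item repeats the primary variable at the same visit against baseline. The SRF endpoint listed under Secondary endpoints is at 7 to 8 months, and the analysis list has no item for it. If baseline in the logistic model were read as baseline SRF status, the covariate would be constant and could not be separated from the intercept.

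**The case against.** The best defence is that this is loose wording. The same paragraph opens with the difference between the two modalities and calls the trial a superiority study, and the objective, endpoint, sample size and hypotheses all agree. Read as arm by change from baseline, the table reduces to arm by SRF status, because the baseline risk of 1 cancels: (22/78)/(39/78) = 22/39 = 0.56, the between-arm relative risk of persistence. A competent statistician would probably run that table. All this stands, and it limits the point to a misspecified sentence. It does not remove it. On that reading the reference to baseline does nothing, and the secondary section shows that the authors separate the two ideas: visual acuity and retinal sensitivity changes are compared between modalities, while SRF at evaluation point 1 is compared with baseline.

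The logistic covariate is worded generically for all categorical secondary endpoints and is not said to be SRF status. A constant covariate would simply drop out. That part is minor.

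A reader might go further and infer that a before-after test would be overwhelmingly significant in both arms, so that the interim analysis could stop the trial on change from baseline alone. The documents do not support this. They name a relative risk and no paired test, so any such p-value would belong to a substituted analysis. Criteria for the termination of the trial also ties early stopping for efficacy to being better than the comparator, which a within-arm change cannot show.

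**Conclusion.** The point holds as an internal contradiction. The primary and interim analysis sentences describe a comparison with baseline that is undefined for SRF absence, reduces to 1 minus the success rate for persistence, and does not test the stated null. This follows from the inclusion criterion and needs no assumed rates.

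The hypothesis, endpoint and sample size are sound on this point. The planned 78 per arm fits the between-arm test, with power of about 0.81 if the rates are 50% and 72%; that pair, the 1.008 factor and the 0.048 level are assumptions. The practical risk is limited because the intent is plain, but the sentence fixes the trial's main test and its interim test and should be corrected. The arm-based analyses under the secondary endpoints do not correct it.

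**What to change.** - **Primary and interim analysis sections:** replace the sentence with a cross-table of treatment arm (half-dose PDT or HSML) by SRF status (absent or persistent) at evaluation visit 1. Report the PDT-versus-HSML relative risk of SRF absence with its 95% CI and a two-sided test of π₁ = π₂, at the O'Brien-Fleming level for each look.
- **Secondary analyses, first item:** replace the comparison of evaluation point 1 with baseline by the between-arm comparison of SRF absence at 7 to 8 months, as Secondary endpoints defines it. Simply deleting the item would leave the list without any SRF analysis.
- **Logistic model:** state that baseline SRF status is not the covariate, since it is constant.

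The cost is wording in the protocol, and in the analysis plan if it carries the same sentence. Sample size, visits and data collection do not change.
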